## Abstract

**Background:**

*Hwa-byung* (HB) is an anger syndrome caused by an inadequate release of accumulated anger that leads to somatic and psychiatric symptoms. As HB results from long-term inadequately treated negative emotions, its symptoms are complex, intractable and concomitant with other psychiatric disorders. Therefore, studies aiming to develop effective and safe treatment options for HB are needed. We plan to conduct a pilot study for a future, full-scale, randomized controlled trial (RCT) of an optimal acupuncture procedure using semi-individualized acupuncture points that consider participants’ personal disposition and type of emotional stress.

**Method/design:**

This randomized, sham-controlled, participant- and assessor-blinded pilot trial aims to determine the study feasibility of acupuncture for HB and to explore its clinical effects and safety. This clinical trial will be conducted with two groups: one treated with real acupuncture and the other with sham acupuncture for 10 sessions over 4 weeks. The experimental group (EG) will receive semi-individualized acupuncture, whereas the control group (CG) will receive sham acupuncture, namely minimal acupuncture on non-acupuncture points. The recruitment, compliance, and completion rate and clinical evaluations, including a Visual Analogue Scale (VAS), the Korean version of the Beck Depression Inventory (BDI), the short form of the Stress Response Inventory (SRI-short form) and the Instrument of the Oriental Medical Evaluation for HB (IOME-HB), will be assessed to evaluate feasibility and possible effects and safety. Four weeks after completing treatment, follow-up assessments will be performed.

**Discussion:**

As this is a pilot study mainly aiming to investigate trial feasibility, the results of this study will be analyzed descriptively and interpreted for the study purposes. Cohen’s *d* will be reported to determine the effect of acupuncture for HB and to enable comparisons with other treatment methods. This protocol is significant in that it provides optimal semi-individualized acupuncture treatment. We expect this study to offer information about the feasibility of this treatment and data about the possible effects and safety.

**Trial registration:**

Clinical Research Information Service (CRIS), Republic of Korea: KCT0001732. Registered on 14 December 2015.

**Electronic supplementary material:**

The online version of this article (doi:10.1186/s13063-017-2399-0) contains supplementary material, which is available to authorized users.

## Background

*Hwa-byung* (HB) is an anger syndrome that is considered a cultural syndrome of Korea. In the *Diagnostic and Statistical Manual of Mental Disorders, version 4* (DSM-IV), HB is listed as a Korean culture-bound syndrome in the glossary of culture-bound syndromes [1], and the disease has been given an independent disease code in the *Korean Standard Classification of Diseases 7* (KCD-7) [2]. Research is currently underway to diagnose HB separately from other mental disorders, as diagnostic criteria change with the culture of the time. Accordingly, the HB Diagnostic Interview Schedule (HBDIS) and the Instrument of Oriental Medical Evaluation for HB (IOME-HB) were developed [3–5]. HB has distinct characteristics that differ from those of other known psychiatric disorders, and is typically accompanied by major depressive disorder (MDD) and generalized anxiety disorder (GAD) [6–8].

The symptoms of HB can be physical and include chest palpitations, flushing, surges of feelings, and lumps in the throat or solar plexus; however, they can also be emotional and include resentment, bitterness, and hard feelings [3]. HB results from anger that has accumulated over a long period of time without being released and is caused both by an individual’s disposition and by repeated stress from a society that imposes unfair and unreasonable restrictions on its members [3, 6, 7]. The prevalence of HB ranges from 4.2% to 13.3% in Korea depending on the age group and region [3, 9] and is reported to be higher in women than in men [10]. Self-perceived HB is relatively prevalent, with a community-based study reporting a rate of 12% [11].

One review study indicated that a multi-disciplinary approach, including religious help and traditional methods, is necessary for the treatment of HB [12]. Another study investigating paroxetine revealed improvements in the symptoms of HB and Hamilton Depression Rating Scale (HAM-D) and State-Trait Anger Expression Inventory (STAXI) scores, but the study was limited to a single-group, open trial [13]. In terms of non-pharmacological treatments, one qualitative study investigating loving-kindness meditation reported therapeutic effects in four of nine participants, partial effects in four participants, and no effect in one participant [14]. Another qualitative study investigating a mindfulness-based stress reduction program indicated improvement in the symptoms of HB and STAXI, Hospital Anxiety and Depression Scale-Anxiety (HAD-A), and Hospital Anxiety and Depression scale-Depression (HAD-D) score [15]; however, these two studies included small sample sizes (9 and 10 participants, respectively) and were single-arm, qualitative studies whose findings are difficult to generalize.

Acupuncture has been used for various psychiatric disorders [16], and its clinical effect against depression [17] and anxiety [18, 19] has been reported in previous studies. For studies on HB, one study reported improvement in the symptoms of HB and Beck Depression Inventory (BDI) score but not in STAXI and State-Trait Anxiety Inventory (STAI) scores [20]. Several studies reported contrasting results, and did not find significant improvement in symptoms of HB or in BDI, STAXI, or STAI scores [21, 22]. These three studies included a control group that received shallow, penetrating, sham acupuncture at non-acupuncture points, which may have contributed to a failure to detect differences between the groups. In addition, the acupuncture used in these studies was focused on traditional eastern philosophy using the Five Elements Theory; thus, the method exhibited limitations in the possible widespread use by global researchers and practitioners. Two studies focused on concurrent symptoms, such as insomnia and anxiety, but remained limited in that one used a waiting list and the other included a single-group, open-trial design [23]. In 2013, clinical guidelines for HB were developed encompassing various studies. The guidelines indicated the limitations as a standardized treatment regimen could not be determined. The clinical guidelines proposed the use of acupuncture to treat HB based on previous evidence and noted that individualized treatment that considers the specific disposition and level and type of stress must be simultaneously provided [24]. Given the need for further research regarding individualized treatment, the present clinical study protocol was developed to use both fixed acupuncture points related to the major symptoms of HB, and variable acupuncture points based on traditional Korean medicine (TKM) principles.

Accordingly, we designed a randomized, sham-controlled, participant- and assessor-blinded, parallel-design pilot study using sham-treatment control and a 1:1 allocation. We will assess the clinical trial feasibility, and explore the effect and safety of acupuncture as a treatment for HB by comparing an experimental group (EG) receiving semi-individualized acupuncture with a control group (CG) receiving sham acupuncture.

## Method/design

### Study design

This study is a randomized, sham-controlled, participant- and assessor-blinded, parallel-design clinical trial. Participants will be assigned to the EG or the CG. The EG will be treated with real acupuncture, whereas the CG will be treated with sham acupuncture.

### Setting of the study

This clinical trial will be conducted at the outpatient department of a university hospital. Public recruitment advertising will be used to recruit participants to voluntarily apply to the trial, and a Korean medical doctor (KMD) will explain the details of the trial and will supply documented explanations. When the participants decide to enroll in the trial, they will be asked to submit written consent and to undergo evaluation to ensure compliance with inclusion/exclusion criteria. Participants who are eligible for the study will be randomly assigned to one of two groups and will receive the planned intervention and evaluation according to their corresponding group. Both groups will receive the intervention for a total of 10 sessions for 4 weeks (two to three sessions per week). A post-treatment assessment will be performed at 4 weeks after visit 1, and the study will be completed 8 weeks after visit 1 (Fig. 1).

**Fig. 1 Fig1:**
[figure not shown]
Trial flowchart

### Recruitment

A participant recruitment document, including the study title, target participants, period, location and contents of the intervention, will be distributed as printed material, newspaper advertisements, and posters displayed at the clinical trial sites.

### Randomization and allocation concealment

An independent statistician will generate a table of random sampling numbers using Strategic Applications Software (SAS) ® Version 9.4 (SAS institute, Inc., Cary, NC, USA). The statistician will place the groups to be assigned into each double-layered, opaque envelope in sequence, seal the envelopes and write the numbers in order. The randomization code will be secured in a double-locked cabinet. As practitioners cannot be blinded by the nature of the intervention, the practitioners will assign the participants to one of the groups by opening the sealed envelopes in order in front of the participants. The opened envelope will be separately stored in a safe. The practitioner will confirm the eligibility before opening the envelope. If the participants do not meet the inclusion criteria, they will be removed from the study, and the randomization will not be performed (the envelope will not be opened). The reason for the lack of randomization will be recorded in a screening log and a Case Report Form (CRF).

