### Blinding of participants and assessors

As this study will use minimal acupuncture for the CG, the practitioners cannot be blinded; however, the participants and assessors will be blinded. Participants will be informed that they will be treated with either classical acupuncture or non-classical acupuncture [28]. Independent assessors who are not in charge of the intervention will ask only the questions necessary to evaluate and record in the CRF and will not know the assigned group throughout the study period. Un-blinding will be considered only under circumstances in which it is necessary for the rights and safety of the participants, including the occurrence of serious adverse effects. In such cases, the researchers will notify the principal investigator (PI) and document the subsequent processes.

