### Clinical outcomes

Clinical outcomes include information regarding the possible effects and safety of acupuncture. The outcome measures regarding clinical effect will be assessed at baseline, week 3, week 5, and week 9. A Visual Analogue Scale (VAS) score for the four major somatic symptoms and two major psychological symptoms of HB will be the primary outcome measure. The major symptoms are chest discomfort, burning sensation of the face or chest, a surge of feeling, sensation of a mass in the throat or in the epigastrium, frequent feelings of unfairness and mortification, and emotional resentment or ill will.

The VAS is widely used for the assessment of variations in the severity of subjective symptoms. Participants mark their symptom severity on a 100-mm straight line whose extreme left end indicates “absence of symptoms” and whose extreme right end indicates “unbearably severe symptoms” [33, 34].

The secondary clinical outcome measures will be the VAS score for subjective anger, the BDI and the short-form of the Stress Response Inventory (SRI-short form). The IOME-HB and serum serotonin levels will be evaluated at baseline and week 5. The BDI is a self-reported inventory to evaluate the severity of depression with 21 questions, including somatic-affective and cognitive-affective factors. Each question is assigned one of 0 to 3 points, and the total score ranges from 0 to 63 [35, 36]. The SRI-short form is used to assess responses to stress. It contains 22 questions, including somatization factors (nine items), depression factors (eight items), and anger factors (five items) [37]. The IOME-HB is used to evaluate the severity of psychiatric and somatic symptoms of each of five types of HB, according to TKM principles, by participants scoring their symptoms using a 5-point Likert scale [4, 5]. Serum serotonin levels will be measured by analyzing the blood drawn from the veins of the arm. We will quantitatively analyze the numbers themselves to see whether there are differences before and after treatment and between groups.

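### The envelope holding the group assignment is opened in front of the participant with no stated safeguard, so the procedure as written does not protect, and may defeat, participant blinding

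*Protocol article*

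**What the plan says.** Protocol article, Randomization and allocation concealment: "The statistician will place the groups to be assigned into each double-layered, opaque envelope in sequence". The envelopes are sealed and numbered. At enrolment, after confirming eligibility, "the practitioners will assign the participants to one of the groups by opening the sealed envelopes in order in front of the participants". The reason given is that practitioners cannot be blinded. The opened envelope is then kept in a safe.

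Protocol article, Blinding of participants and assessors: "the practitioners cannot be blinded; however, the participants and assessors will be blinded". On what participants hear: "Participants will be informed that they will be treated with either classical acupuncture or non-classical acupuncture". On disclosure: "Un-blinding will be considered only under circumstances in which it is necessary for the rights and safety of the participants". The Abstract, the last paragraph of the Background and the Study design section also describe the trial as participant- and assessor-blinded.

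**The concern.** The unblinded practitioner opens the assignment while the person who must stay blinded is present. That practitioners cannot be blinded explains why they may see the group. It does not explain why the participant should be there when it is revealed.

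Three things depend on participant blinding here:

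- **The clinical scales.** Participants produce the primary scores, so blinding the assessor does little to prevent biased responses.
- **The acceptability rule.** Feasibility outcomes calls acupuncture acceptable for a full-scale study if the effect size exceeds 0.2 in at least three of six major symptoms, and those symptoms are measured by the VAS.
- **The blinding index.** Feasibility outcomes uses it to judge whether the blinding procedure needs modification. The Discussion uses it to help choose the control for future research. The index may show that blinding failed but cannot say where. A failure at the envelope could be read as a failure of minimal acupuncture.

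**Working it through.** This is a point of procedure, so the check is mainly to set the sections side by side. The only design figure, a total of 26 participants, is not power-based, and the point does not depend on it.

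**Step 1. What protects the assignment, and when** (Randomization and allocation concealment)

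| Stage | Stated protection |
|---|---|
| Before opening | Double-layered opaque sealed envelope; code in a double-locked cabinet |
| At opening | None stated; participant present |
| After opening | Opened envelope stored separately in a safe |

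The envelope conceals the sequence until it is opened. Neither it nor the later storage covers the moment of opening. The section says that the group is inside and mentions no code. Even a slip using the neutral terms given to participants (classical or non-classical) would tell a participant who read it which of the two applied.

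**Step 2. Compare with the blinding section.** Participants are to stay blinded, and disclosure is reserved for rights and safety. Both sections can hold only if the content is hidden from the participant at opening, and the article does not state that condition.

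**Step 3. Which outcomes are exposed** (Clinical outcomes)

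| Measure | Who supplies the score |
|---|---|
| VAS, six major symptoms (primary) | Participant: "Participants mark their symptom severity on a 100-mm straight line" |
| BDI | Participant: "The BDI is a self-reported inventory to evaluate the severity of depression with 21 questions" |
| IOME-HB | Participant, on a 5-point Likert scale |
| SRI-short form | 22 questions; mode of completion not stated |
| Serum serotonin | Laboratory |

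Self-report is therefore explicit for the VAS, BDI and IOME-HB. For the SRI-short form it is only an inference. The exclusion of people who cannot understand or answer questionnaires supports it.

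**Step 4. Can the bias be sized?** Not from the documents. They give neither the number of participants who might see the slip nor the effect of knowing the arm on ratings. What can be examined is how the acceptability rule responds to a shift from any source.

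Inputs: 26 participants allocated 1:1, so 26 / 2 = 13 per arm. With no true effect, the standard error of Cohen's d is about √(2/13) = 0.39. A simulation used normal data, pooled-SD d and 20,000 runs per setting. The between-symptom correlation and the size of the shift, taken in favour of real acupuncture on all six symptoms, are assumptions.

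| Assumed shift | Rule met, correlation 0.3 | 0.5 | 0.7 |
|---|---|---|---|
| 0 | 31% | 32% | 33% |
| 0.2 SD | 60% | 58% | 55% |
| 0.3 SD | 73% | 69% | 67% |

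The first row is a property of the rule at this sample size and has nothing to do with the envelope. The other rows show that the rule is sensitive to a modest average shift. They do not estimate what the envelope step does.

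**The case against.** The strongest reply is that opening an envelope before someone is not the same as showing them what is in it. The article does not say that the slip is shown, read aloud or handed over. If only the practitioner reads it, or if it carries a code, the two sections agree. A reader might infer that the sections flatly contradict each other, or that every participant is unblinded at entry. The text supports neither.

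Four further points:

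- **Level of detail.** The wording or shielding of a slip may be left to a fuller protocol or site instruction. This does not dispose of the point, because the article does not merely omit a detail. It states a step that puts the participant at the opening.
- **Practitioner cues.** The practitioner's reaction to the slip is not a separate argument. Practitioners are unblinded by design, and the same practitioner treats both groups (Treatment of control group), so cues can arise at any of the ten sessions. Only the visibility of the content is specific to this step.
- **Planned detection.** The blinding index is meant to test the blinding procedure as well as the sham, so misattribution is possible but not certain. Descriptive analysis of a pilot also lowers the stakes. Detection still does not prevent disclosure.
- **The witness.** Opening before the participant lets a second person see that envelopes are used in order. This has value, because the practitioner also confirms eligibility and gives the treatment. The objection stands against any remedy in which the practitioner simply opens the envelope alone, and the fix should allow for it.

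A reader might also take the 55% to 73% in the simulation as the harm caused by this step. It rests on an assumed shift of 0.2 to 0.3 SD that has no source in the documents.

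**Conclusion.** The point holds as an unprotected blinding step. The unblinded practitioner opens an envelope containing the assignment in front of the participant, no safeguard for the content is stated, and the article claims participant blinding throughout. As written, the procedure does not protect that blinding and may defeat it.

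The exposure is to the participant-marked primary VAS, the BDI and the IOME-HB, to the acceptability rule built on the VAS, and to the interpretation of the blinding index. The size of any bias is unknown. The conclusion assumes only that the slip is readable by someone who sees it, which is the plain meaning of placing the group in the envelope. If the site already codes or shields the slip, saying so resolves the point. It should be corrected now, because the Trial status section says recruitment is under way and a disclosure cannot be undone.

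**What to change.** Remove the reference to opening the envelope before the participant. State instead that, after confirming eligibility, the practitioner opens the next numbered envelope so that its content is neither visible nor disclosed to the participant, and signs and dates the envelope before it is stored. The content may be protected by opening out of sight, by shielding the card or by using a coded card.

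Cost: one sentence in the protocol and the site instruction, plus a signature and date on each envelope. The options differ slightly:

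- **Shielded card:** the participant can still witness that envelopes are opened in order.
- **Opening out of sight:** that witness is lost, and the signed, dated and stored numbered envelopes provide the audit trail instead.
- **Coded card:** a key is needed, and the unused envelopes must be prepared again.

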### Sample size calculation

This study aims to evaluate clinical trial feasibility and to investigate basic information about effects and safety of acupuncture for the treatment of HB, rather than to satisfy hypothesis testing. Therefore, the sample size was not decided based on power calculations but based on the precision of mean and standard deviation (SD), the rationale of feasibility, and ethical issues that prohibit over-recruitment of participants. We ensured that the sample size exceeded the minimal number needed to assure the validity of the mean, SD and effect size and rationale of feasibility [25] and considered the study period and research budget [26, 27]. Accordingly, a sample size of 26 participants was estimated.

### Blinding of participants and assessors

As this study will use minimal acupuncture for the CG, the practitioners cannot be blinded; however, the participants and assessors will be blinded. Participants will be informed that they will be treated with either classical acupuncture or non-classical acupuncture [28]. Independent assessors who are not in charge of the intervention will ask only the questions necessary to evaluate and record in the CRF and will not know the assigned group throughout the study period. Un-blinding will be considered only under circumstances in which it is necessary for the rights and safety of the participants, including the occurrence of serious adverse effects. In such cases, the researchers will notify the principal investigator (PI) and document the subsequent processes.

## Characteristics of participants

### Inclusion criteria

Men and women who are aged 20 to 65 yearsMeet the diagnostic criteria of the HBDIS: participants should have at least three of the four major symptoms (including chest discomfort, burning sensation of the face or chest, a surge of feeling, and sensation of a mass in the throat or in the epigastrium), one of two major psychological symptoms (including feelings of unfairness and mortification, and emotional resentment or ill will), two of four related somatic symptoms, and two of three related psychological symptoms. The symptoms should be related to stress, should cause psychosocial hypo-function, and should not be caused by a medical disorderProvide written informed consent after being informed of the objectives and details of the clinical trial and agreeing to participate in the trial

